# Safety and efficacy of umbilical cord-derived Wharton’s jelly compared to hyaluronic acid and saline for knee osteoarthritis: study protocol for a randomized, controlled, single-blind, multi-center trial

**DOI:** 10.1186/s13018-021-02475-6

**Published:** 2021-05-31

**Keywords:** Umbilical cord, Wharton’s jelly, Knee osteoarthritis, Regenerative medicine, Biologics, Randomized controlled trial, Extracellular vesicles, Exosomes, Growth factors, Hyaluronic acid

## Abstract

**Background:**

Osteoarthritis (OA) is the most common joint disorder in the United States of America (USA) with a fast-rising prevalence. Current treatment modalities are limited, and total knee replacement surgeries have shown disadvantages, especially for grade II/III OA. The interest in the use of biologics, including umbilical cord (UC)-derived Wharton’s jelly (WJ), has grown in recent years. The results from a preliminary study demonstrated the presence of essential components of regenerative medicine, namely growth factors, cytokines, hyaluronic acid (HA), and extracellular vesicles, including exosomes, in WJ. The proposed study aims to evaluate the safety and efficacy of intra-articular injection of UC-derived WJ for the treatment of knee OA symptoms.

**Methods:**

A randomized, controlled, single-blind, multi-center, prospective study will be conducted in which the safety and efficacy of intra-articular administration of UC-derived WJ are compared to HA (control) and saline (placebo control) in patients suffering from grade II/III knee OA. A total of 168 participants with grade II or III knee OA on the KL scale will be recruited across 53 sites in the USA with 56 participants in each arm and followed for 1 year post-injection. Patient satisfaction, Numeric Pain Rating Scale, Knee Injury and Osteoarthritis Outcome Score, 36-Item Short Form Survey (SF-36), and 7-point Likert Scale will be used to assess the participants. Physical exams, X-rays, and MRI with Magnetic Resonance Observation of Cartilage Repair Tissue score will be used to assess improvement in associated anatomy.

**Discussion:**

The study results will provide valuable information into the safety and efficacy of intra-articular administration of Wharton’s jelly for grade II/III knee osteoarthritis. The results of this study will also add to the treatment options available for grade II/III OA as well as help facilitate the development of a more focused treatment strategy for patients.

**Trial registration:**

ClinicalTrials.gov, NCT04711304. Registered on January 15, 2021

## Background

Osteoarthritis (OA) is the most common joint disorder in the United States of America (USA), affecting approximately 12% of US adults aged between 25 and 74 years [1]. By 2030, the number of US adults with arthritis is expected to reach 67 million, leading to a continuous increase in the number of total knee replacement surgeries [2–4]. While total knee replacement surgeries have shown advantages, avoiding or delaying such surgery is usually desirable, for medical reasons and health care system perspective [5]. The long-term outcomes after total knee replacement surgeries for patients with grade II or III knee OA on the Kellgren-Lawrence (KL) scale are worse compared to patients with grade IV OA [6, 7]. Additionally, conventional treatment modalities, including activity modification, physical therapy, and pharmacological agents such as non-steroidal anti-inflammatory drugs, corticosteroids, viscosupplementation, and narcotics, have limitations and potential side effects [8–16]. Thus, there is a need for alternative intervention for patients with grade II or III knee OA.

Interest in the use of biologics for regenerative medicine applications has increased over the last decade [17–22]. To be compliant with the relevant laws and regulations in the US biologics that adhere to the US Food and Drug Administration regulation of Human Cells, Tissues, and Cellular and Tissue-Based Products (HCT/P’s) regulated under title 21, part 1271 of the Code of Federal Regulations, must meet all the conditions under section 361 of Public Health Safety Act to be regulated solely under this section [17, 23]. According to this regulation, HCT/P’s must meet the criteria of being minimally manipulated, for homologous use only, not to be combination products, to have no systemic effect, and to be non-dependent on the metabolic activity of the living cells [17]. Despite the increased use, there is insufficient literature assessing the amount of growth factors (GFs), cytokines (CKs), hyaluronic acid (HA), and extracellular vesicles (EVs), including exosomes, present in these products, and more specifically, umbilical cord (UC)-derived Wharton’s jelly (WJ). In addition, there is limited or no literature assessing the safety and efficacy of UC-derived WJ products via a randomized, controlled, multi-center study.

We formulated a novel UC-derived WJ product that has been shown to contain the essential components of regenerative medicine, namely GFs, CKs, HA, and EVs [24]. In addition, the Wharton’s jelly has been reported to contain high amounts of extracellular matrix components, including collagen, hyaluronic acid, and sulfated proteoglycans, required to improve the treatment effect [24]. That study was an essential preliminary step to better characterize the WJ formulation before performing clinical trials to determine its safety and efficacy including providing symptomatic relief to patients with grade II or III knee OA.

The goal of the proposed study is to evaluate the safety and efficacy of intra-articular injection of UC-derived WJ for the treatment of knee OA symptoms. We hypothesize that there will be no difference in the outcomes in patients receiving injection of UC-derived WJ, HA, or saline in terms of safety. We also hypothesize that patients receiving intra-articular injection of WJ will show an improvement in their overall satisfaction, Numeric Pain Rating Scale (NPRS), Knee Injury and Osteoarthritis Outcome Score (KOOS), and cartilage formation over a period of 1 year compared to the baseline visit. Our null hypothesis is that there is no difference in patients receiving either WJ, HA, or saline, and no difference between baseline and after treatment within each treatment group over a period of 1 year.

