#### Inclusion criteria

Consenting adult patients over the age of 18 years diagnosed with grade II or grade III (mild or moderate) OA on the KL scale (in only one knee) will be considered for this study along with the following inclusion criteria:
Body mass index (BMI) of <50kg/m^2^.Ability to comply with requirements of study visits.Pain score of 4 or more on the Numeric Pain Rating Scale (NPRS).Female patients must be abstinent, surgically sterilized, or postmenopausal.Premenopausal females must have a negative pregnancy test, on contraceptive measures, and do not anticipate pregnancy during the duration of the study.Males with premenopausal female partners will have to take contraceptive measures for the duration of the study.Be willing and capable of giving written informed consent to participate.Be willing and capable of complying with study-related requirements, procedures, and visits.

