We anticipate that this study will demonstrate that intra-articular administration of WJ is safe. Some minimal adverse effects can be observed. The adverse events associated with the intra-articular administration of Wharton’s jelly will be similar to inherent risks associated with any intra-articular injection. These include pain and/or reaction at the injection site, failure of therapy to work as expected, infections, potential for contamination of the product, and unknown or unexpected reactions, including but not limited to immunogenic reactions, tumorigenic reactions, and development of autoimmune disorders. We also anticipate that patients suffering from grade II/III OA will experience improvement in their pain, function, quality of life, and overall satisfaction. In addition, we foresee that articular cartilage formation will increase over the 1-year period of the study in comparison with the baseline visit. This study has several limitations. The present investigation was designed as single-blinded rather than double-blinded. The concept of a double-blinded study was abandoned as the treating investigators can easily detect the difference in viscosity between the injectables used. Nevertheless, most of the endpoints in the study will be patient-reported, thus reducing the bias from the unblinded investigators. Another limitation of the study is the utilization of only one HA formulation: we are aware that the HA formulations with different molecular weights or cross-linking are available. Thus, the results from this study may not be applicable to other HA formulations. In conclusion, the results of this study will add to our understanding of the treatment options available for grade II/III OA and help facilitate the development of a more focused treatment strategy for patients with grade II/III OA.

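### The only directional efficacy hypothesis is improvement from baseline in the WJ arm, which an inert product could meet; the planned between-arm comparisons have no direction or priority over it

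*Protocol article*

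**What the plan says.** The last paragraph of the Background in the protocol article contains three statements.

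- Safety: "there will be no difference in the outcomes in patients receiving injection of UC-derived WJ, HA, or saline in terms of safety". This compares the arms.
- Efficacy: "patients receiving intra-articular injection of WJ will show an improvement in their overall satisfaction", and likewise in NPRS, KOOS and "cartilage formation over a period of 1 year compared to the baseline visit". This compares WJ patients with themselves.
- Null: "Our null hypothesis is that there is no difference in patients receiving either WJ, HA, or saline", followed in the same sentence by "no difference between baseline and after treatment within each treatment group over a period of 1 year".

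The Discussion repeats the baseline framing. The authors expect patients to improve in pain, function, quality of life and satisfaction, and write that "we foresee that articular cartilage formation will increase over the 1-year period of the study in comparison with the baseline visit".

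Between-arm comparison does appear in other places. The Abstract (Methods) and Study design set WJ against HA and saline. In Assessment points, the secondary endpoints cover NPRS, KOOS and MOCART both from baseline and between groups. Patient satisfaction, one of the two primary endpoints, is listed there with no comparator. None of these places says that WJ is expected to do better than saline or HA.

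Entry requires "Pain score of 4 or more on the Numeric Pain Rating Scale (NPRS". Under Study interventions, HA and saline patients may switch to WJ after the 3-month visit.

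**The concern.** A trial with a saline arm exists to separate the effect of the product from everything else that happens to patients after an injection. The hypothesis that carries the efficacy claim does not use that arm. It is met if WJ patients are better at follow-up than at baseline, and that can happen with no product effect at all. Most endpoints are patient-reported, so placebo response is to be expected. Patients are also selected on a pain score above a threshold, so mean NPRS tends to fall on re-measurement.

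The null adds to this by listing within-arm change next to the between-arm difference without ranking them. The hypothesis runs to 1 year, but controls may leave their arm from month 3. If many do, the uncontrolled baseline comparison would be the easiest 1-year result to report. As worded, the trial could report its efficacy hypothesis as confirmed with a WJ minus saline difference of zero.

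**Working it through.** **1. The plan's own figure.** Sample size and statistical analysis gives a KOOS difference of 8 to 10 units, two-sided alpha 0.05, a stated β of 90% (read here as power of 90%), and at least 40 per group, raised to 56. The raise implies a loss of 1 − 40/56 = 28.6%. No SD is given, and the text does not say whether the 8 to 10 units are between arms or within an arm. The 40 therefore cannot be reproduced, only solved backwards for the SD, with z-values 1.960 + 1.282 = 3.242.

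- Two-sample reading: SD = δ·√(n/2)/3.242. For δ = 8, 8 × 4.472/3.242 = 11.0. For δ = 10, 13.8. With the t distribution these become 10.9 and 13.6.
- Paired, within-arm reading: SD = δ·√n/3.242. For δ = 8, 8 × 6.325/3.242 = 15.6. For δ = 10, 19.5.

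The 40 fits either reading, so the sample size does not settle which comparison was meant.

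**2. Chance of meeting the hypothesis with an inert product.** Assumptions, none of them from the document: WJ equals saline; both arms gain m KOOS points by month 3; m is 8 or 5; the SD of change covers both readings above and extends to 20. The within-WJ test is a one-sample t-test with n = 40, 39 degrees of freedom and critical value 2.023. Its noncentrality is m·√40/SD. For m = 8 and SD = 13.6 this is 8 × 6.325/13.6 = 3.72, giving a rejection probability of 95%.

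| SD of change | Source of SD | Both arms gain 8 | Both arms gain 5 |
|---|---|---|---|
| 10.9 | two-sample, δ = 8 | 99.5% | 81% |
| 13.6 | two-sample, δ = 10 | 95% | 62% |
| 15.6 | paired, δ = 8 | 89% | 51% |
| 19.5 | paired, δ = 10 | 72% | 35% |
| 20 | upper value assumed | 69% | 34% |

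A two-sided WJ versus saline test rejects in 5% of such trials whatever the common gain. Simulation with 20,000 runs at SD 13.8 gave 4.7% to 4.9%.

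**3. Regression to the mean on NPRS alone.** Assume an NPRS SD of 2, a source-population mean of 4 to 6, a test-retest correlation of 0.5 to 0.8, and entry at 4 or more. With no placebo effect, mean NPRS falls by 0.1 to 0.8 points. A within-arm test with n = 40 then shows improvement in 8% to 76% of trials, against a nominal 2.5% in that direction. The effect is small to moderate and depends heavily on the assumed inputs.

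**The case against.** The strongest reply is that the controlled comparison is already in the plan. The Abstract, the Study design, the first half of the null and the secondary endpoints all compare arms, and an undirected null is the normal partner of the two-tailed test that the article specifies. This stands. A reader might infer from the Background that the saline and HA arms will be ignored, or that no between-arm test is planned; the documents do not support that.

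A reader might also take the null as one joint statement, so that a change in any arm, even saline, would reject it and count as efficacy. The sentence can equally be read as two nulls listed together, matching the two comparisons under the secondary endpoints. The article gives no decision rule under which rejecting either part counts as efficacy. A full protocol or analysis plan may say which test supports the claim.

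Three further limits stand. The NPRS entry rule causes regression to the mean directly only in NPRS; it reaches KOOS only through correlation and does not bear directly on MOCART, so placebo response carries most of the argument. The common gains of 8 and 5 points are assumptions. The illustration is at month 3, whereas the hypothesis runs to 1 year.

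The reply does not remove the point. The hypothesis is written out in the article, so it is not a detail left to another document, and it names the wrong comparator for a placebo-controlled efficacy claim. The undirected between-arm statements are given no precedence over it.

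**Conclusion.** The point holds in limited form. The only directional efficacy hypothesis is a within-WJ change from baseline, repeated in the Discussion. The planned between-arm comparisons have neither direction nor priority, so the stated hypothesis can be met by an inert product.

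The size depends on an assumed placebo change and an SD that the document does not give. Quoting only the SDs from the two-sample reading (95% to 99.5% for 8 points, 62% to 81% for 5) would be selective, because the paired reading gives 72% to 89% and 35% to 51%. Across SDs of 10.9 to 20 the range is 69% to 99.5% for 8 points and 34% to 81% for 5. Every value is far above the 5% of a WJ versus saline test, so the conclusion does not depend on which reading is right.

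**What to change.** - Reword the efficacy hypothesis as a difference between arms in change from baseline: WJ versus saline first, then WJ versus HA, at month 3. That is the time point on which the sample size is based, and it comes before crossover is offered.
- State the between-arm null and the within-arm null separately.
- Treat within-arm change as supportive description and not as evidence of efficacy.
- Bring the expectations in the Discussion into line.

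No extra visits, patients or measurements are needed, because NPRS and KOOS are already recorded at baseline and month 3. MOCART is scheduled only at baseline and 1 year, so the cartilage hypothesis cannot move to month 3. It should also be worded between arms, with crossover acknowledged. The real cost is that a pre-post improvement alone can no longer be called efficacy. The choice of month 3 as the main efficacy time point, in place of the 1-year horizon in the Background, also has to be made openly.

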## Methods and analysis

This study protocol is reported in accordance with the Standard Protocol Items: Recommendations for Intervention Trials (SPIRIT) criteria [25, 26].

### Study setting

This multi-center study involves up to 53 sites consisting of health care centers, community clinics, and academic hospitals in the USA.

### Study design

This is a randomized, controlled, single-blind, multi-center, prospective study in which the safety and efficacy of intra-articular UC-derived WJ are compared to HA (control) and saline (placebo control) in patients suffering with knee OA. The participants in the treatment arm will receive a 2-mL intra-articular injection of UC-derived WJ (GeneXSTEM, BioIntegrate Inc., Lawrenceville, GA, USA, diluted with 1:1 sterile normal saline). The participants in the control arm and placebo arm will receive 4 mL HA (Monovisc®—4 mL injection with 22mg/mL HA, Anika Therapeutics, Bedford, MA, USA) and 4 mL of sterile normal saline, respectively. Patients in the HA group or saline group will be offered the opportunity to cross over to the Wharton’s jelly group after 3 months, as a method to aid in study recruitment and retention (Fig. 1).

**Fig. 1 Fig1:**
[figure not shown]
Summary of the trial design

### Participants

A total of 168 patients with grade II or III knee OA on the KL scale will be recruited with 56 patients in each arm. Participation will be discussed with patients who meet the inclusion criteria. The patients will be given the opportunity to read an informed consent form (ICF) and obtain answers to all questions before considering participation at the enrollment/baseline visit.

#### Inclusion criteria

Consenting adult patients over the age of 18 years diagnosed with grade II or grade III (mild or moderate) OA on the KL scale (in only one knee) will be considered for this study along with the following inclusion criteria:
Body mass index (BMI) of <50kg/m^2^.Ability to comply with requirements of study visits.Pain score of 4 or more on the Numeric Pain Rating Scale (NPRS).Female patients must be abstinent, surgically sterilized, or postmenopausal.Premenopausal females must have a negative pregnancy test, on contraceptive measures, and do not anticipate pregnancy during the duration of the study.Males with premenopausal female partners will have to take contraceptive measures for the duration of the study.Be willing and capable of giving written informed consent to participate.Be willing and capable of complying with study-related requirements, procedures, and visits.

#### Exclusion criteria

Patients will be excluded from the enrollment in the study if they meet any of the following exclusion criteria:
Patients who have taken any pain medication including non-steroidal anti-inflammatory drugs (NSAIDs) within 2 weeks prior to study injection datePatients who use anticoagulants, have a substance abuse history, and/or fail to agree not to take any knee symptom-modifying drugs during the course of the study without discussing and reporting the use to the site principal investigator and study teamPositive on special tests and/or stability tests on physical examPatients with intra-articular injection of any drug including corticosteroids and viscosupplementation in the index knee in the last 3 monthsSurgery on the index knee within the last 6 monthsTraumatic injury to the index knee within the last 3 monthsPlanned elective surgery during the course of the studyHistory of organ or hematologic transplantation, rheumatoid arthritis, or other autoimmune disordersPatients on immunosuppressive medications/treatmentPatients with a diagnosis of non-basal cell carcinoma within the last 5 yearsPatients with knee infection or who used antibiotics for knee infection within the last 3 monthsPatients who participated in another clinical trial or treatment with any investigational product within the last 30 days prior to the inclusion in the studyFemale patients who are breastfeeding or are pregnant or desire to be pregnant or become pregnant during the course of the studyContraindications to radiographic or MRI imagingSerious neurological, psychological, or psychiatric disordersOther medical conditions including any malignancies determined by the site principal investigator as interfering with the studyInjury or disability claims under current litigation or pending or approved workers’ compensation claims

Participants can voluntarily withdraw from the study at any time. Withdrawal from the study will not affect the patient’s access to other treatments nor will the patient be subjected to any sanctions. Participation in the study may be terminated if continued participation in the study is not in the subject’s best interest, according to the principal investigator’s opinion or if the subject withdraws participation. Determination of therapy cessation and need of explanation will be performed by the principal investigator (PI) based on the standard medical practice. Any patient who suffers an adverse event whether or not related to treatment may withdraw voluntarily.

### Randomization

Participants will be assigned to a treatment group using sealed opaque envelopes coded with an alphanumeric identifier to ensure consecutive allocation of envelopes. Block randomization across all sites will be used to ensure even distribution to each group of 1:1:1 allocation to the 3 study arms—WJ, HA, and saline.

### Study interventions

After completion of visit 1 (preliminary/baseline), and determination of patient’s eligibility to be enrolled in the study, participants will be randomized into one of the three arms of the study and be scheduled for the procedure visit. At this visit, the participants will either receive an intra-articular injection of WJ (treatment), HA (control), or saline (placebo control). Following the procedure, the participants will be periodically followed for 1 year. After the 3-month follow-up visit, patients injected with HA or saline will be offered the opportunity to cross over to the WJ group. If they decide to cross over, they will receive an injection of WJ and will follow the schedule of events for the WJ injection group beginning immediately after the injection follow-up visit.

### Assessment points

Assessments for the study period will begin at visit 1 (preliminary/baseline). The patients will be assessed using the inclusion/exclusion criteria for eligibility in the study. The participants will then undergo a physical exam (PE) on the knee diagnosed with grade II/III OA, as well as a baseline plain radiograph for an up-to-date OA grade on the KL scale and a T2-weighted MRI to obtain a Magnetic Resonance Observation of Cartilage Repair Tissue (MOCART) score. The participants will also be required to complete baseline case report forms (CRFs) including the Numeric Pain Rating Scale (NPRS), Knee Injury and Osteoarthritis Outcome Score (KOOS), and patient satisfaction/survey, SF-36. Demographic information and medical history will also be collected. The participants will then be assessed for any adverse events at visit 2.2, immediately following their respective intra-articular injection, and at their procedure visit (visit 2.1) and be re-assessed for pain using the NPRS. Through visit 3 (24 h follow-up), visit 4 (48 h follow-up), and visit 5 (1 week follow-up), patients will be reassessed for pain using the NPRS. On visit 5 (1 week follow-up), visit 6 (6 weeks follow-up), and visit 7 (3 months follow-up), participants will undergo another PE as well as have their NPRS, KOOS, and 7-point Likert scale recorded. Plain radiographs will be taken on visits 6 and 7. At this point of the study, patients in the HA or saline arms will be offered the opportunity to cross over to the WJ arm and will follow the schedule of events beginning at visit 2.2. On visit 8 (6 months follow-up) and visit 9 (1 year follow-up), patients will undergo a PE as well as have their NPRS, KOOS, 7 point Likert scale, and SF-36 taken and recorded. In addition, plain radiographs will be taken again followed by an MRI on visit 9 for a MOCART score. All participants will have the opportunity to report any adverse events at each visit or at any time within the study.

The following are the primary endpoints:
To determine the safety of umbilical cord-derived Wharton’s jelly formulation (GeneXSTEM™)To assess the patient satisfaction

The following are the secondary endpoints:
To assess the change in patient-reported outcome measures, NPRS and KOOS, from baseline and between the groups at different time pointsTo assess the cartilage formation via MOCART at 1 year time point and compare it from baseline and between the groups

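### Only HA and saline patients are offered WJ at 3 months, so patient masking of WJ versus control ends there, and the 6-month and 1-year patient-reported WJ contrasts are open-label in a trial described as single-blind

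*Protocol article*

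**What the plan says.** All references are to the protocol article.

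- **Masking.** Study design: "This is a randomized, controlled, single-blind, multi-center, prospective study". The Discussion explains that double-blinding was given up because "treating investigators can easily detect the difference in viscosity between the injectables used".
- **Mitigation.** The Discussion answers that limitation by saying that "most of the endpoints in the study will be patient-reported, thus reducing the bias from the unblinded investigators". It sets no time limit on this.
- **Who gets the offer.** Study design: "Patients in the HA group or saline group will be offered the opportunity to cross over to the Wharton’s jelly group after 3 months", with the stated purpose "as a method to aid in study recruitment and retention". Study interventions: "After the 3-month follow-up visit, patients injected with HA or saline will be offered the opportunity to cross over to the WJ group". Assessment points says the same of visit 7: "patients in the HA or saline arms will be offered the opportunity to cross over to the WJ arm".
- **What follows acceptance.** Study interventions: "If they decide to cross over, they will receive an injection of WJ". These patients then follow the WJ schedule.
- **Later outcomes.** Assessment points schedules NPRS, KOOS, the 7-point Likert scale and SF-36 at visit 8 (6 months) and visit 9 (1 year). NPRS and KOOS are secondary endpoints, compared between groups at several times. Patient satisfaction is a primary endpoint, and no follow-up visit is named for it in that section.

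**The concern.** A single-blind label with open investigators means that the patient is the one kept unaware. An offer of WJ made only to patients who have not had WJ is itself information about allocation. After it, the people who complete the questionnaires can know whether they received the novel product.

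Pain, function, quality-of-life and satisfaction ratings are open to expectation. If the 6-month and 1-year contrasts are reported under the single-blind label, a reader will credit them with a protection they do not have. The Background's hypotheses run over 1 year and include a null of no difference between the arms, so these later contrasts are part of what the trial sets out to show. The article nowhere says that the masked phase ends.

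**Working it through.** No stated figure is in dispute, so the check is to read the sections together.

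**Step 1: who is masked.** Study design says that one party is blind. The Discussion says that the investigators are not. The masked party is therefore the patient.

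**Step 2: what the offer reveals.** Study design, Study interventions and Assessment points agree that the offer goes to the HA and saline arms only. Its stated use as a recruitment aid implies that patients hear of it before they join.

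| Patient | Learns at the 3-month offer | Still hidden by the offer |
|---|---|---|
| HA or saline, accepts | Was not given WJ; now knowingly gets WJ | Whether the first injection was HA or saline |
| HA or saline, declines | Was not given WJ | Whether the injection was HA or saline |
| WJ, knows of the scheme | Gets no offer, so can infer WJ | Nothing |
| WJ, does not know of the scheme | Nothing | Allocation |

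The first two rows follow directly from the text. The third rests on prior knowledge, which the recruitment purpose implies; no consent text is shown to confirm it.

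**Step 3: which contrasts are affected.** There are three pairwise contrasts. Two involve WJ (against HA and against saline), and both lose patient masking. HA against saline is not unmasked by the offer.

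**Step 4: which data are affected.** Visits on the original schedule, from Assessment points:

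| Instrument | Follow-up up to and including visit 7 | Follow-up after the offer |
|---|---|---|
| KOOS | Visits 5, 6, 7 | Visits 8, 9 |
| 7-point Likert | Visits 5, 6, 7 | Visits 8, 9 |
| NPRS | Procedure visit and visits 3 to 7 | Visits 8, 9 |
| SF-36 | None (baseline only) | Visits 8, 9 |

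For KOOS and the Likert scale, 2 of 3 + 2 = 5 follow-ups come after the offer. For SF-36 it is 2 of 2, so no masked follow-up on that instrument exists. Everything recorded after a crossover injection is also open, because the patient knows it is WJ.

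**Step 5: does the mitigation hold?** Patient-completed forms keep an unblinded investigator from doing the rating. They give masked outcome data only while the patient is masked. Up to the offer both conditions hold; after it, only the first does.

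**Step 6: is the 3-month comparison affected?** Study design puts the offer after 3 months, and Study interventions puts it after the 3-month visit. Assessment points lists the visit 7 examination, questionnaires and radiographs before it turns to the offer. The three agree that assessment comes first. The sample size rests on the 3-month change in KOOS, so that comparison stands as masked on the text given.

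**The case against.** **The crossover is a declared choice.** It has stated reasons (recruitment and retention, and in the Discussion the uncertain evidence for HA), and the comparison on which the trial is sized comes before it. This stands. The point is not that crossover is wrong, but that the masking claim is not limited to the period in which it holds. The intent-to-treat statement in the Discussion does not help, since analysing patients as randomised does not restore masking.

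**The Discussion sentence is about investigator bias only.** Fairly read, it makes no claim about patient expectation, and self-completed forms still keep the investigator from rating after 3 months. That part stands. But the sentence is offered as the answer to single-blinding, without a time limit, and the same Discussion does not mention that patient masking is lost.

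**A reader might infer that every patient learns the allocation and that all three arms are unmasked.** The text does not support this. The offer reveals WJ versus not-WJ, and patients who decline still do not know whether they had HA or saline.

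**A reader might infer that the 3-month outcome is unmasked too**, because Assessment points places the offer at visit 7. The order within that section and the wording of the other two sections point the other way. Finer sequencing within the visit is detail that an article may leave to the full protocol.

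**A reader might want a false-positive rate.** One can be produced by assuming a shift in reported KOOS and back-solving an SD from the sample size. But the protocol supplies neither the shift nor an SD, the sizing calculation concerns 3 months, and controls who cross over knowingly receive WJ, so they do not behave like controls who know they are controls. Such a rate would be illustrative only, and none is relied on here.

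**Conclusion.** The concern holds in a limited form. As written, the single-blind description does not apply to patient-reported WJ-versus-control contrasts at 6 months and 1 year: two of the three pairwise contrasts, at two visits, on four instruments, plus patient satisfaction if it is assessed then.

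For HA and saline patients this follows directly from the text. For WJ patients it assumes that they know of the scheme in advance, which the recruitment purpose implies but the article does not document. Even without that assumption, control patients know they did not receive WJ, which is enough to leave the contrast unmasked on one side.

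The size and direction of any resulting bias cannot be derived from the document. HA versus saline, the 3-month comparison, and outcomes that are not patient-reported lie outside this conclusion.

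**What to change.** 1. In Study design, Assessment points and the Discussion, state that patient masking of WJ versus control ends with the 3-month crossover offer.
2. Treat the 3-month between-group comparison as the masked one, and label the 6-month and 1-year patient-reported WJ contrasts as open-label.
3. In the Discussion, limit the mitigation based on patient-reported endpoints to data up to 3 months.
4. As a safeguard, state in Study interventions and Assessment points that all visit 7 questionnaires, the examination and adverse event recording are completed and locked before crossover is mentioned.

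An alternative that may suggest itself is to ask patients in all arms the same question at visit 7 and disclose allocation only to those who want WJ. It is not recommended: it would unmask WJ patients who say yes and leave a self-selected masked remainder.

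The cost is a wording amendment, with no extra visits, staff or patients and no change to the crossover itself. The downside is that the 6-month and 1-year claims become weaker.
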